#### Control group

Patients in the control group receive standard care, consisting of home-based unsupervised wrist exercises, and upon request or recommendation by their clinician, a referral for specialised hand physiotherapy or occupational therapy. An overview of simple exercises for the three main motions in the wrist (palmar/dorsal flexion, pronation/supination and radial/ulnar deviation) is provided on paper, together with an explanation of exercises by the clinician. Patients are instructed to perform controlled movements up to a point that cause a stretch but no pain. Patients are instructed to practise these movements three to five times daily, approximately 10–15 min per session. This regimen has been developed in cooperation with specialised hand and wrist physiotherapists and occupational therapists, and is most reflective of current standard practice. All patients referred to physiotherapy are instructed to perform active exercises without load. The number of physiotherapy visits will be registered prospectively.

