### Outcome measurements

Standard demographic information including age, sex, fracture type according to the Arbeitsgemeinschaft für Osteosynthesefragen/Orthopaedic Trauma Association fracture classification,^39^ and the type of treatment is obtained directly after inclusion. Follow-up visits take place at 2, 6, and 12 weeks postoperatively or after cast removal, for operatively or conservatively treated patients, respectively. A timeline of the trial is shown in figure 3. The primary outcome measure, which is the validated Patient-Rated Wrist Evaluation (PRWE) questionnaire is completed by patients at all follow-up visits.^40 41^ The active ROM is measured in degrees using an analogue universal goniometer. ROM and grip strength are measured in both hands, where grip strength is measured in kilograms, using an analogue hand dynamometer (Baseline, Fabrication Enterprises, White Plains, New York, USA). The maximum value of two measurements with 5 min rest in between is used for analysis. All measurements are performed by a clinician blinded to group allocation that has been specifically trained for this trial, and is experienced in taking ROM and strength measurements in daily practice.

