### Data analysis

The primary outcome is the PRWE score at 6 weeks. This outcome is represented as the change in outcome scores from T0 to T2 (delta, T2–T0). An intention-to-treat analysis is performed, and any missing data are imputed. Data will be analysed using a two-sided t-test or the Mann-Whitney U test, depending on normality of the distribution.

For the secondary continuous outcomes (PRWE score at 2 and 12 weeks, ROM, grip strength, pain scores), a repeated measures analysis of variance will be performed, where group assignment (game group vs control group) is the between-subjects factor, and time of visit (baseline, 2, 6 or 12 weeks follow-up) is the within-subjects factor. In case of a non-normal distribution, generalised estimating equations will be used. An intention-to-treat analysis will be performed, and any missing data will be imputed using multiple imputation. Other (secondary) functional outcomes are analysed as a percentage of the unaffected wrist. Bonferroni correction is applied to all secondary outcomes to correct for multiple tests. Therefore, p values of <0.0045 will be considered statistically significant.

Baseline data and secondary outcomes include categorical data such as fracture type and treatment type. These data will be analysed using the Χ^2^ test, and outcomes will be presented as the differences in frequencies. P values of <0.05 are considered statistically significant. Treatment adherence is measured using a self-reported diary. The number of exercise sessions and the total duration of exercising are continuous variables that will undergo quantitative and qualitative synthesis using a two-sided t-test or a Mann-Whitney U test as appropriate.

The diaries that are handed in after the trial period are analysed for the percentage of days the diary is completed and the total estimated time of exercising. In the intervention group, these data are also compared with the total time of exercising as registered within the game. In addition, should not all diaries be completed, the number of diaries handed in after the study period is registered. These data are then analysed using the Χ^2^ test, and outcomes will be presented as the difference in frequencies.

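### Analysing ROM and grip strength as a percentage of the unaffected wrist is valid but gives away precision, mainly for small motions and noisy grip; adjusting for both wrists' baselines would recover it

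*Protocol article*

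**What the plan says.** Under Outcome measurements, "ROM and grip strength are measured in both hands, where grip strength is measured in kilograms". On the instrument: "The active ROM is measured in degrees using an analogue universal goniometer". On replicates: "The maximum value of two measurements with 5 min rest in between is used for analysis".

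Under Data analysis, ROM and grip strength are among the continuous secondary outcomes for which "a repeated measures analysis of variance will be performed, where group assignment (game group vs control group) is the between-subjects factor"; visit (baseline, 2, 6 or 12 weeks) is the within-subjects factor, and no covariate is named. The scale is then set: "Other (secondary) functional outcomes are analysed as a percentage of the unaffected wrist". For the secondary outcomes, "p values of <0.0045 will be considered statistically significant".

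The motions trained in the trial are "palmar/dorsal flexion, pronation/supination and radial/ulnar deviation" (Control group), so they include one pair with a small range.

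**The concern.** The tested quantity is one measured value divided by another. Goniometer or dynamometer error in the healthy wrist therefore becomes error in the outcome. A few degrees matter little against a wide arc but are a large share of a narrow one. Dividing also assumes that the affected side rises in exact proportion to the unaffected side. Measurement error flattens the observed relation, so division over-corrects. A covariate lets the data set that weight.

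The affected wrist's own baseline enters the planned model only as one level of visit, not as a covariate. What is at stake is the chance of detecting a real difference in ROM or grip at a strict threshold, in a trial sized only for the primary questionnaire.

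**Working it through.** **The article's own figures.** With an SD of 15.9, a difference of 11.5, two-sided alpha 0.05 and power 90%, the normal approximation gives 41 per group and the exact t calculation 42 (power 0.906 at 42), as stated. The threshold 0.0045 is 0.05/11 = 0.004545. No power is stated for ROM or grip.

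**First-order variances.** Let A and U be the measured affected and unaffected values, m the ratio of their means, and ρ their correlation.
- Percentage (times the squared mean of U): sA² + m²sU² − 2mρ·sA·sU
- Unaffected wrist as covariate: sA²(1 − ρ²)
- Difference: (m·sU − ρ·sA)², never negative to this order

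**Example, small motion (all values assumed).** Mean U 20 degrees, true between-patient SD 4, affected side 70% of unaffected with between-patient SD 0.15, and equal error on both sides.
- No error: sA² = 0.49·16 + 0.0225·416 = 17.2; sU² = 16; covariance = 0.7·16 = 11.2. Percentage: 17.2 + 7.84 − 15.68 = 9.36. Covariate: 17.2 − 11.2²/16 = 9.36. They are equal, and both are well below the unadjusted 17.2.
- Error of 4 degrees: sA² = 7.84 + 9.36 + 16 = 33.2; sU² = 32. Percentage: 33.2 + 15.68 − 15.68 = 33.2, no better than the unadjusted value. Covariate: 33.2 − 11.2²/32 = 29.28. Ratio 33.2/29.28 = 1.13.

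With the same formulas, a 70-degree motion (SD 10, affected side 70%) with 4 degrees of error gives a ratio of 1.01. Grip (mean 32 kg, SD 11, affected side 55%) with 4 kg of error also gives 1.01.

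In terms of coefficients of variation a (affected) and u (unaffected), the excess is (u − ρa)²/[a²(1 − ρ²)]. For a from 0.20 to 0.50, u from 0.13 to 0.33 and ρ from 0.2 to 0.7, it runs from 0 (a 0.50, u 0.25, ρ 0.5) to (0.33 − 0.04)²/(0.04·0.96) = 219% (a 0.20, u 0.33, ρ 0.2). The formula shows direction; the size depends on the inputs.

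**Simulated power.** Inputs as above; assumed effects of 15% (20-degree motion), 10% (70-degree motion) and 12% (grip) of the unaffected mean; 42 per group; 3,000 runs; one follow-up visit; threshold 0.05/11. The comparison is a t-test on A/U against A with U as covariate, without the affected baseline. The deficit is either a proportion of U or additive.

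| Outcome | Error | Proportional: percentage → covariate | Additive: percentage → covariate |
|---|---|---|---|
| 20 degrees | 2 | 0.659 → 0.708 | 0.667 → 0.754 |
| | 4 | 0.204 → 0.335 | 0.205 → 0.356 |
| | 5 | 0.096 → 0.217 | 0.114 → 0.249 |
| 70 degrees | 2 | 0.528 → 0.511 | 0.508 → 0.520 |
| | 4 | 0.429 → 0.425 | 0.428 → 0.449 |
| | 6 | 0.323 → 0.339 | 0.323 → 0.354 |
| Grip, kg | 1 | 0.722 → 0.672 | 0.594 → 0.718 |
| | 2 | 0.564 → 0.585 | 0.504 → 0.645 |
| | 4 | 0.253 → 0.375 | 0.273 → 0.401 |

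The gaps for noisy small motions and noisy grip exceed the first-order result because a noisy denominator also skews the ratio.

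**Adding the affected wrist's baseline.** If its partial correlation with follow-up, given U, is p, residual variance is multiplied by 1 − p²: 0.91, 0.75 and 0.51 for p = 0.3, 0.5 and 0.7 (assumed). A separate simulation with other assumed inputs (42 per group, 0.0045, one visit) compared the plain percentage with both baselines as covariates: 22-degree motion with 3 degrees of error, 0.32 → 0.46; flexion, 0.63 → 0.76; grip with 2 kg of error, 0.52 → 0.70.

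**The case against.** The strongest reply is that nothing here is an error. The percentage is a prespecified scale that patients and clinicians read easily, it asks its own clinical question (recovery relative to the patient's own wrist), and randomisation keeps the comparison valid. That stands: the issue is efficiency alone.

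Four stronger readings are tempting, and the documents do not support them.
- *The covariate always has more power.* The first-order result suggests so, but the simulation contradicts it. With 1 kg of grip error and a proportional deficit, the percentage is ahead (0.722 against 0.672), and for a 70-degree motion the two are about level.
- *The ratio is the main cause of lost power everywhere.* When both analyses adjust for the affected baseline, one set of runs gave flexion 0.54 by percentage and 0.56 by covariate, and grip with 1 kg of error 0.83 and 0.81. There, most of the gain comes from the baseline, which a percentage outcome could use too.
- *The plan ignores baseline.* It does not: baseline is a level of visit. The single-visit simulations are therefore not the power of the planned repeated measures test. In one run that analysed change in percentage from baseline, the 22-degree motion with 3 degrees of error still went from 0.34 to 0.65 under the full adjustment.
- *Secondary power is known to be low.* The article states no expected effect or power for ROM or grip and does not rank them above other secondary outcomes. Trained, experienced assessors may keep error small; how small is not stated.

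Applying the percentage sentence to ROM and grip is an inference from its loose opening word *Other*. It is the natural reading, since no other outcome is described as measured in both hands.

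**Conclusion.** The point holds as a modest improvement in the precision of secondary outcomes. Replacing the percentage by an unaffected-wrist covariate alone gains, at the 0.0045 threshold, about 5 to 15 power points for a 20-degree motion with 2 to 5 degrees of error. For grip with 4 kg of error it gains about 12 to 13 points. It is about neutral for large motions (−2 to +3 points) and can lose about 5 points for grip if error is very small and the deficit strictly proportional. Adding the affected wrist's baseline brings a further gain for all of these, by an amount set by its unknown correlation with follow-up.

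All sizes rest on assumed means, SDs, errors and effects and on a single follow-up visit; the direction for small motions does not depend on whether the deficit is proportional or additive. There is no bias, and the primary outcome, the 42 per group and the total of 92 are unaffected.

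**What to change.** Replace the percentage sentence under Data analysis with one stating that ROM and grip strength of the affected wrist at follow-up are analysed in degrees or kilograms, with the affected wrist's baseline value and the unaffected wrist's baseline value as covariates. Percent of the unaffected wrist is then reported descriptively. Baseline moves from being a level of visit to being a covariate for these outcomes. Naming ROM and grip in that sentence also removes the doubt over what *Other* covers.

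The cost is one sentence and no new measurements, because both hands are already measured and baseline is already a planned visit for these outcomes. The downside is that the tested effect is in degrees or kilograms, not percent, with a possible slight loss from dropping the ratio if grip were measured almost without error.

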This multicentre, randomised controlled clinical trial aims to evaluate the effects on functional outcomes of a wearable-controlled serious game played on a smartphone or tablet, that is developed specifically for wrist rehabilitation. This is compared with the current standard treatment following distal radius fracture. This study hypothesises that the use of the game may lead to a higher treatment adherence by improving motivation and adding entertainment to exercises, thus increasing self-efficacy. It is therefore hypothesised that patients recovering with use of the game will show a greater improvement in patient-rated functional outcomes compared with standard treatment. Second, this study aims to compare active range of motion (ROM), grip strength, treatment adherence, pain scores and to measure the effects on return to work between the two treatment strategies.

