**Figure 3 F3:**
[figure not shown]
Schematic timeline of the study showing the randomisation and follow-up planning, as well as the outcomes measured during each visit. ORIF, open reduction internal fixation; PRWE, Patient-Rated Wrist Evaluation; ROM, range of motion.

Patients in both study arms complete a questionnaire, that was specifically developed for this trial, on their self-efficacy, experiences and perceived effectiveness of their exercise programme. Pain scores on a Visual Analogue Scale are recorded, and patients are asked about the frequency, if any, of visits to a physiotherapist or occupational therapist. In addition, partial or complete return to work, or to normal functioning if patients were currently unemployed, is registered. Patients are reminded by the researcher to fill out their exercise diary at every follow-up visit and are asked to return their completed exercise diary at 6 weeks of follow-up. In the intervention group, the data on exercise frequency and duration, as well as ROM, will also be retrieved from the serious game. The frequency reported by patients in this group will be compared with the data from the game application, which stores all exercise data including frequency, duration and the ROM measured.

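### Categorical secondary outcomes are given two incompatible significance limits, 0.0045 and 0.05, so the stated multiplicity correction does not hold as written

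*Protocol article*

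**What the plan says.** The Data analysis section of the protocol article treats the secondary outcomes in consecutive paragraphs.

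- The paragraph on continuous secondary outcomes ends with a general rule and its consequence: "Bonferroni correction is applied to all secondary outcomes to correct for multiple tests. Therefore, p values of <0.0045 will be considered statistically significant".
- The following paragraph opens with "Baseline data and secondary outcomes include categorical data such as fracture type and treatment type". It assigns these data to the chi-square test, says that "outcomes will be presented as the differences in frequencies", and then sets a second limit: "P values of <0.05 are considered statistically significant".

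Return to work appears elsewhere in the article. The last paragraph of the Introduction includes among the secondary aims "to measure the effects on return to work between the two treatment strategies". Under Outcome measurements, "partial or complete return to work, or to normal functioning if patients were currently unemployed, is registered". As recorded, this is a categorical variable.

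**The concern.** Both rules name secondary outcomes. The first covers all of them without exception. The second covers the categorical ones and is not limited to baseline data. A categorical secondary outcome therefore has two limits that differ by a factor of about 11 (0.05/0.0045 = 11.1).

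Any p value between 0.0045 and 0.05 can then be called significant or not, depending on which sentence is followed. Return to work is the outcome most exposed, because the Introduction attributes the cost of these injuries mainly to lost productivity, so a result on it is likely to be emphasised. If the choice between the limits is left open until results are known, the result could influence it. If the looser limit is used, the correction that the plan announces no longer protects the set of secondary outcomes at the level it was built for.

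**Working it through.** **Inputs.** From Data analysis: 0.0045 for all secondary outcomes, and 0.05 for the categorical data. From the Introduction and Outcome measurements: at least one categorical secondary comparison, return to work. Assumption: k, the number of categorical secondary tests judged at 0.05. The article does not give it, so k = 1 is used as the smallest case that matters.

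**Step 1. Reproduce the plan's limit.** Bonferroni limit = 0.05/m.

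| m | 0.05/m | rounded |
|---|---|---|
| 10 | 0.00500 | 0.0050 |
| 11 | 0.004545 | 0.0045 |
| 12 | 0.004167 | 0.0042 |

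Only m = 11 gives 0.0045. The limit is correct for 11 tests.

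**Step 2. Error across the secondary tests under one limit.**

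- Bonferroni bound: 11 × 0.0045 = 0.0495.
- Independent tests: 1 − (1 − 0.0045)^11 = 1 − 0.9516 = 0.0484.

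The first rule, applied alone, holds the error at about 5%.

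**Step 3. The same error when one categorical outcome is judged at 0.05.**

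| Where the categorical test sits | Bound | Independent tests |
|---|---|---|
| One of the 11 | 10 × 0.0045 + 0.05 = 0.0950 | 1 − 0.9955^10 × 0.95 = 0.0919 |
| In addition to the 11 | 11 × 0.0045 + 0.05 = 0.0995 | 1 − 0.9955^11 × 0.95 = 0.0960 |

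The result is about 9% to 10% either way, roughly double the intended level. Independence is a working assumption. The bound holds under any dependence, and positive correlation would bring the figure below the independent value. It cannot fall below 5%, because the one test at 0.05 uses that amount by itself. The guarantee of 5% is lost; the actual error depends on the correlation.

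**Step 4. Effect on one result.** Suppose return to work gives p = 0.02. Since 0.0045 < 0.02 < 0.05, it is not significant under the first rule and significant under the second.

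**The case against.** The strongest reply is that the 0.05 was meant for baseline comparisons. The only examples in that paragraph, fracture type and treatment type, are baseline variables. Treatment type is also a stratification factor in the Randomisation section, so neither can be an effect of the game. On this reading the general rule governs every outcome and nothing is inflated. This may well be the intent, but the sentence expressly includes secondary outcomes and nothing narrows the limit that follows. If that was the intent, the wording misstates it and needs the same correction.

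It is also fair to say that the Data analysis section never names return to work or assigns it a test, and that the abstract does not list it among the secondary outcomes. Its place under the 0.05 rule is therefore an inference from its being a categorical secondary aim. It appears to fall under both limits; the article does not state that it does.

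A reader might go further in three ways that the document does not support.

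- **A much larger error.** Adding four tests at 0.05 to the 11 gives 1 − 0.9955^11 × 0.95^4 = 0.225. This requires return to work to be tested separately at three visits, which no section says. It also requires diary return to be judged at 0.05, although the diary paragraph states no limit. And it treats repeated observations of the same patients as independent.
- **A fault in not listing the 11 tests.** A journal article may leave that list to the full protocol or analysis plan.
- **A fault in choosing Bonferroni.** It is a valid method. Comparing power at 0.0045 with power at 0.05 contrasts correction with no correction; it does not show what another valid correction would gain.

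**Conclusion.** The contradiction stands. Categorical secondary outcomes are subject to 0.0045 in one paragraph and 0.05 in the next, and no text resolves the two. If even one such outcome is judged at 0.05, the error across the secondary outcomes rises from about 5% to about 9% to 10%. That figure assumes one such test, 10 or 11 others at 0.0045, and independence. It applies only if the 0.05 is used for an outcome; it would be too strong to conclude that the error is certainly uncontrolled, because the baseline-only reading remains possible.

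The consequence is limited. The primary outcome has its own two-sided 0.05, and the sample size does not depend on this point. The continuous secondary outcomes named in the repeated-measures paragraph (PRWE at 2 and 12 weeks, range of motion, grip strength and pain) sit clearly under 0.0045. What is in doubt is how categorical secondary results will be labelled. It is worth correcting because the remedy is short, but it does not threaten the trial's main conclusion.

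**What to change.** Replace the two limits with one rule:

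1. The corrected limit applies to every secondary outcome, categorical ones included.
2. The limit is 0.05/m, where m is the actual number of secondary tests. If m is 11, 0.0045 stands. If return to work turns out to be a twelfth test, the limit becomes 0.05/12 = 0.0042.
3. The unadjusted 0.05 applies only to the primary outcome.
4. Baseline variables are described by group without significance tests. Treatment type in particular is balanced by the stratified block randomisation.

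With 11 tests all at 0.0045, the bound returns to 0.0495.

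As an option, Holm's step-down procedure at 0.05 over the same set of tests gives the same error control as Bonferroni and is never less powerful. It is an improvement; the contradiction can be removed without it.

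The cost is two or three sentences and no new data. The small downside is that categorical outcomes face a stricter limit than 0.05. The change should be made before results by group are seen.

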### Sample size calculation

The primary outcome is the PRWE questionnaire outcome score after 6 weeks of treatment. This questionnaire has been validated previously,^40^ and has a minimal clinically important difference of 11.5, with 1.5 for the pain subscale and 10 for the function subscale.^41^

An elaborate and important Cochrane review on the effect of physiotherapy after distal radius fractures reports only three studies comparing a regular physiotherapy regimen with an unsupervised home-exercise programme.^15^ These comparisons are relevant here, since the use of this serious game can be compared with an unsupervised home-exercise programme. Only one of these three trials reports patient-rated functional outcomes in addition to ROM or grip strength values.^18^ This study looks into the effects of a progressive home-exercise programme, compared with the effect of 12 physiotherapy sessions over a 6-week period in patients with an operatively treated distal radius fracture. They found a positive effect in favour of the home-exercise programme, with PRWE scores of 18.5 (SD 15.9) for the home-exercise group, compared with 36.1 (SD 13.9) in the physiotherapy group after 6 weeks.^18^

As a result, using the SD of 15.9, for a two-sided t-test in two groups with an alpha of 0.05, a power of 90% (1–beta=0.9), an allocation ratio of 1:1, this leads to necessary group sizes of 42 patients per group to detect a clinically relevant difference of 11.5 points at 6 weeks. With a 10% dropout rate, a total of 92 patients are needed for this trial.

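### Secondary outcomes: the single-step Bonferroni limit of 0.0045 is valid, but Holm's step-down gives the same 5% family-wise control, never rejects less, and costs one sentence once the family is named

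*Protocol article*

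**What the plan says.** The Data analysis section of the protocol article sets the rule in two sentences: "Bonferroni correction is applied to all secondary outcomes to correct for multiple tests. Therefore, p values of <0.0045 will be considered statistically significant". They close the paragraph on continuous secondary outcomes, whose model is introduced with the words "For the secondary continuous outcomes (PRWE score at 2 and 12 weeks, ROM, grip strength, pain scores), a repeated measures analysis of variance will be". The number of tests behind 0.0045 is not given.

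The next paragraph says "Baseline data and secondary outcomes include categorical data such as fracture type and treatment type", assigns these data to the chi-squared test, and then states "P values of <0.05 are considered statistically significant". The comparison of exercise sessions and exercise time (adherence) follows that sentence and carries no limit of its own.

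The Introduction gives the secondary aims: "this study aims to compare active range of motion (ROM), grip strength, treatment adherence, pain scores", and also return to work.

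The primary outcome, PRWE at 6 weeks, is a single test outside this correction. The Sample size calculation section powers that test only.

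**The concern.** Single-step Bonferroni makes every test in the family pass the limit that a step-down procedure requires only of the smallest p-value. Holm's procedure starts at the same limit and then relaxes it, with no loss of family-wise error control. Any outcome that passes at a later Holm step but misses 0.0045 is therefore given up without buying protection.

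What is at stake is the power of the secondary aims, in a trial sized for one primary comparison. These outcomes all describe recovery of the same wrist, and the trial's hypothesis is that one mechanism, better adherence, drives it. If the game works, several outcomes may move together, and that is where a step-down rule helps most.

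**Working it through.** **Inputs from the article.** Limit 0.0045 (Data analysis). Primary-outcome design: 42 per group, SD 15.9, difference 11.5 points, two-sided alpha 0.05, power 90% (Sample size calculation).

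**Assumptions.** The article gives no effect size or SD for ROM, grip strength or pain, and no correlation between outcomes. I borrow the PRWE effect, d = 11.5/15.9 = 0.723, add a smaller d = 0.5, let 3, 6 or all 11 outcomes truly differ, and take an equal correlation of 0.5. Each outcome is treated as a simple two-group comparison, not as the planned repeated measures model.

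**1. The stated limit.** 0.05/10 = 0.0050, 0.05/11 = 0.00455, 0.05/12 = 0.00417. Only 11 tests round to 0.0045. Upper bound on the family-wise error: 11 × 0.0045 = 0.0495. With independent tests: 1 − (1 − 0.0045)^11 = 0.0484. The rule does what it claims.

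**2. Single-test power at 42 per arm.** Noncentral t with 82 degrees of freedom and noncentrality d√(42/2). For d = 0.723 the noncentrality is 3.31. Power is 0.906 at 0.05, in line with the planned 90%, and 0.652 at 0.0045. The normal approximation used below gives 0.68 at 0.0045, slightly higher.

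**3. Holm on 11 ordered p-values.** The limits are 0.05/11, 0.05/10, …, 0.05/1: 0.00455, 0.00500, 0.00556, 0.00625, 0.00714, 0.00833, 0.0100, 0.0125, 0.0167, 0.0250, 0.0500. Testing stops at the first failure.

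- No limit is below 0.05/11, so every Bonferroni rejection is also a Holm rejection.
- The first limit is the Bonferroni limit, so the probability of at least one rejection is identical.
- If m₀ null hypotheses are true, the first false rejection is made at a limit no larger than 0.05/m₀. Its probability is at most m₀ × 0.05/m₀ = 0.05, whatever the dependence.

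**4. Size of the gain.** Simulation with 11 two-sided z-tests, correlation 0.5, 400,000 runs per row. Power is the average per real effect.

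| d | Real effects | Bonferroni | Holm | At least one rejection (both) |
|---|---|---|---|---|
| 0.72 | 3 of 11 | 0.68 | 0.70 | 0.90 |
| 0.72 | 6 of 11 | 0.68 | 0.72 | 0.96 |
| 0.72 | 11 of 11 | 0.68 | 0.80 | 0.98 |
| 0.5 | 3 of 11 | 0.29 | 0.30 | 0.53 |
| 0.5 | 6 of 11 | 0.29 | 0.32 | 0.67 |
| 0.5 | 11 of 11 | 0.29 | 0.36 | 0.76 |

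With d = 0.72 and 6 real effects, the simulated family-wise error over the 5 true nulls is 2.0% (Bonferroni) and 3.2% (Holm). Over correlations from 0 to 0.7, Holm's power at d = 0.72 runs from 0.70 to 0.70 (3 real), 0.73 to 0.72 (6 real) and 0.83 to 0.79 (11 real). In every run Holm kept all Bonferroni rejections.

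**5. Can the family be read off the text?** Counting each named continuous outcome once: PRWE at 2 and at 12 weeks (2), grip strength (1) and pain (1) make 4. ROM adds 1, 3 or 6, depending on whether it is one outcome, three motion pairs or six directions. The totals are 5, 7 or 10. None of these is 11, so something else must be in the family, or the tests are counted in another way.

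**The case against.** The strongest reply is that nothing here is wrong. Bonferroni is prespecified, valid under any dependence and correctly calculated. No stated figure, sample size or primary conclusion changes with Holm, and a conservative rule for secondary outcomes is a legitimate choice. That stands, and it is why this is offered as an improvement only. It does not remove the case for Holm, which gives the same guarantee and is never less powerful.

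The gain can also be small, and this stands too. With 3 to 6 real effects out of 11 it is about 1 to 4 percentage points. A reader might take the rise from 0.68 to 0.80 as the typical benefit, but that figure needs all 11 outcomes to differ by 0.72 SD, and the article supports no such assumption for ROM, grip strength or pain.

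A reader might also infer that the change is free. It is not quite: Bonferroni pairs directly with simple simultaneous confidence intervals and a fixed limit that can be applied outcome by outcome, and Holm does not. The article plans no such intervals, so this cost is minor.

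Finally, a reader might infer from the word all in the Bonferroni sentence that every secondary outcome, adherence included, is held to 0.0045. The text does not settle this. The following paragraph puts categorical secondary outcomes next to p < 0.05, and adherence comes after that sentence. A change of method alone would leave this open, because Holm needs a defined family as much as Bonferroni does.

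**Conclusion.** The point holds as a low-cost improvement. The 0.0045 limit is sound and consistent with 11 tests; Holm on the same family gives equal family-wise protection and at least as many rejections. At 42 per arm the expected gain in average power per real effect is about 1 to 4 points when 3 to 6 of 11 outcomes truly differ, and about 7 points (d = 0.5) to 12 points (d = 0.72) if all 11 do. The chance of finding at least one effect does not change. These sizes rest on assumed effects, an assumed correlation of 0.5 and two-group tests; that Holm never rejects less rests on none of them.

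The documents do not support calling the Bonferroni rule an error, or saying that the trial's conclusions are at risk. The article does leave two limits, 0.0045 and 0.05, that both appear to reach secondary outcomes. They must be reconciled before either procedure can be applied without dispute.

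**What to change.** Before unblinding, in the Data analysis section or the statistical analysis plan:

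1. List the secondary tests that make up the family (the 11 implied by 0.0045), stating how ROM is split and which term of each repeated measures model is tested.
2. State whether the categorical secondary outcomes and the adherence comparisons belong to that family, and restrict the p < 0.05 sentence to whatever lies outside it.
3. Replace the fixed limit with wording such as: The listed secondary outcomes are tested with the Holm step-down procedure at a family-wise 0.05, and Holm-adjusted p-values are reported. If step 2 changes the number of tests, the Holm limits follow from the new number.

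The cost is one sentence and a short list, with no extra patients or data and no effect on the primary test or sample size. If simultaneous confidence intervals are wanted later, those that match Holm are less simple than Bonferroni intervals.
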